7.1.3 Sample Storage and Shipment

Serology serum samples should be stored at approximately minus -20º C or lower, until analysis.

The Day 0, Day 21 and Day 42 samples and reserve samples will be sent to Medicago R&D Inc. in eight (8) shipments; Day 0 samples, Day 0 back-up samples, Day 21 samples, Day 21 back-up samples, Day 42, Day 42 back-up samples, Day 228 samples and Day 228 back-up samples. Once the analytical laboratory confirms the receipt of the first shipment, the second set of aliquots of reserve samples may be sent. No samples should be shipped on a Friday or the weekend.

All shipments must be accompanied by the shipping manifest provided by the study Sponsor.

The shipment will be delivered to the following address:

[name]

Manager, Analytical Development

Medicago R&D Inc

[name]

[name]

[contact] Ext. 150

7.2 Clinical Supplies

Medicago R & D Inc. will supply the clinical study site with all necessary HAI testing supplies (sampling tubes, aliquot tubes, aliquot labels, aliquot storage and shipping boxes and accompanying manifests). Disposable syringes, needles and SST tubes will not be supplied by the study Sponsor. Complete study sample management procedures are described in the Study Laboratory Manual provided by the Sponsor.

8.0 ASSESSMENTS METHODS AND ENDPOINTS

8.1 Safety Endpoints, Immunogenicity Endpoints, and Assessments Methods

8.1.1 Endpoints

8.1.1.1 Primary Endpoints

Safety and tolerability endpoints to be collected include solicited symptoms, oral temperature and local injection site pain, erthyema (redness) and swelling. Systemic complaints reasonably anticipated to occur as a result of receipt of the test articles will be graded as mild, moderate or severe as follows: headache, muscle aches, joint aches, fatigue, chills, feelings of general discomfort, or uneasiness, swelling in the axilla, groin, neck or chest. These signs and symptoms will be measured and reported by each study subject from the time of study vaccine administration to (Day 0 – Day 1 and Day 2 – Day 7) seven days post-vaccination.

- - Percentage, intensity and relationship of immediate complaints for at least 2 hours post-vaccination)
  - Percentage, intensity and relationship to vaccination of solicited local and systemic signs and symptoms 7 days following each dose of study vaccine
  - Percentage, intensity and relationship of solicited and unsolicited local and systemic signs and symptoms 21 days following each dose of study vaccine
  - Occurrence of all adverse events and serious adverse events
  - The number and percentage of subjects with normal and abnormal haematological and biochemical values at Screening, Day 21 and 42
  - The number and percentage of subjects with normal and abnormal urine values at Screening, Day 21 and 42

Any adverse events or serious adverse event will be collected throughout the course of the study. The collection of adverse events will begin following the signature of the Informed Consent Form.

Any clinical laboratory test result that meets the criteria for an AE in the absence of appropriate and/or adequate clinical diagnosis should be reported as an A/E, unless the result is considered normal for the current trial subject population.

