- Perform vital signs measurements, including oral temperature, heart rate and resting blood pressure. Blood pressure will be taken after the participant has been in a seated position for 3 minutes. Blood pressure should be taken by cuff (manual or automated is acceptable), although the same method should be used throughout the study. Screening measurement of blood pressure may be repeated one time following a 5-minute resting period in a seated position, if judged necessary. All values are to be recorded in the source documentation with the reason for repeating. Pre-vaccination blood pressure results must be found to be within the following ranges: systolic blood pressure is systolic, ≤150 mmHg and diastolic ≤90 mmHg. Heart rate or pulse must be > 40 beats per minute (bpm) and <100 bpm.
- Screening blood samples (20 mL) for biochemistry and haematology analysis will be taken.
- Perform urinalysis (dip stick) on all subjects.
- Perform urine pregnancy testing all females of child-bearing potential participants. If screening and treatment are not done on the same day, an additional pregnancy test must be done prior to treatment on Day 0.

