11.0 STATISTICAL METHODS AND DETERMINATION OF SAMPLE SIZE

11.1 Statistical Methods

Data analysis will be performed at Anapharm Inc.

An interim clinical study report analyzing safety and immunogenicity at 42 days post-vaccination will be completed.

All descriptive and inferential statistical analyses will be performed using SAS^®^ Version 8.2 or higher statistical software. Descriptive statistics for continuous variables will consist of the mean, median, geometric means (where appropriate), standard deviation, minimum, and maximum values. For categorical variables, the number and percent of each category will be displayed. Frequency tables for categorical variables may be performed using Microsoft^®^ Office Excel 2003 or higher version.

For the analysis of safety and immunogenicity endpoints, a two-sided alpha level of 5% will be used. All statistical tests will be two-tailed unless otherwise stated. No attempt will be made to control type I error rate inflation attributable to multiple comparisons.

Demography will be compared among treatment groups using Fisher’s exact test for categorical factors and the Kruskal-Wallis test for continuous factors.

The calculations and statistical analyses will be further described in a statistical analysis plan.

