11.1.2.2 Safety

Safety endpoints will be compared (each vaccine dose level versus placebo) using Fisher’s exact tests.

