11.3 Determination of Sample Size and Power Calculation

The sample size is limited as this is a first-in-human study. Nevertheless, 12 subjects per treatment groups will allow observing an adverse reaction having 10% incidence with about 72% probability. An adverse reaction having 5% incidence will be observed with about 46% probability.

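### Haematology and biochemistry results are compared between arms only as normal versus abnormal by Fisher's exact test, which at 12 per arm has about 2% power for an assumed 1 SD shift; baseline-adjusted dose-minus-placebo estimates should be added

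*Protocol*

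**What the plan says.** Clinical laboratory results are among the primary safety measures (Protocol, Synopsis and 2.1.1). Section 8.1.1.1 gives the form of the endpoint: "The number and percentage of subjects with normal and abnormal haematological and biochemical values at Screening, Day 21 and 42". The Synopsis has the same item.

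Section 11.1.2.2 states the comparison: "Safety endpoints will be compared (each vaccine dose level versus placebo) using Fisher’s exact tests". The Synopsis and section 2.1.2 repeat it. Section 11.1 sets the level: "For the analysis of safety and immunogenicity endpoints, a two-sided alpha level of 5% will be used". It adds: "No attempt will be made to control type I error rate inflation attributable to multiple comparisons". Section 11.1 also plans means, medians, standard deviations and ranges for continuous variables, and leaves further description to a statistical analysis plan.

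The numeric data exist. Section 5.1.5.1 says "Screening blood samples (20 mL) for biochemistry and haematology analysis will be taken", and section 7.1 repeats the sampling at Day 21 and Day 42. No section gives the screening value a role in the comparison.

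Section 11.3 sizes the trial only for the chance of seeing an event: "12 subjects per treatment groups will allow observing an adverse reaction having 10% incidence with about 72% probability". It continues: "An adverse reaction having 5% incidence will be observed with about 46% probability".

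**The concern.** Each haematology and biochemistry result is a number with that subject's own pre-vaccination number beside it. The plan reduces it to two categories before comparing arms. Healthy volunteers start mostly inside the reference range, so a whole group can move appreciably while few of its members cross a limit. With 12 per arm, Fisher's test needs a large difference in counts before it signals.

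In a first-in-human dose-escalation trial, a consistent dose-related shift in a laboratory value is something the sponsor would want to estimate. A row of non-significant Fisher tests could be read as reassurance that the test cannot give. The small sample does not force this loss; discarding the measured values does.

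The protocol treats other numeric outcomes differently. Fold rise in titre is compared by ANOVA on log-transformed data (11.1.2.1), and cell-marker data by t-tests or ANOVA (8.1.2).

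**Working it through.** **Inputs from the protocol.** 12 per arm and four arms (11.3, Table 4); two-sided 5% with no multiplicity adjustment (11.1); Fisher's exact test, each dose versus placebo (11.1.2.2).

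**Assumptions not in the protocol.** Normal values (after log transformation if skewed); a reference range covering the central 95%, so 5% abnormal on placebo; no dropout; a mean shift of d SD in the vaccine arm; correlation r between screening and follow-up of 0 to 0.8.

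**The protocol's own figures.** P(at least one event in 12) = 1 − (1 − p)^12.
- p = 0.10: 1 − 0.9^12 = 0.718, stated as about 72%.
- p = 0.05: 1 − 0.95^12 = 0.460, stated as about 46%.

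Both reproduce.

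**How many abnormal values Fisher needs (12 v 12).**
- 4/12 v 0/12: p = 0.093, not significant.
- 5/12 v 0/12: p = 0.037, significant.
- 6/12 v 1/12: p = 0.069, not significant.

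**Abnormal rate after a shift.** P(Z > 1.96 − d) + P(Z < −1.96 − d). At d = 1 this is 0.1685 + 0.0015 = 0.170, or about 2 of 12 subjects expected (12 × 0.170 = 2.04).

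**Fisher power**, summed over all 13 × 13 tables, placebo rate 5%:

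| Shift | Abnormal, vaccine arm | Power |
|---|---|---|
| 0 | 5% | 0.02% (type I error) |
| 1 SD | 17.0% | 2.2% |
| 1.5 SD | 32.3% | 20% |
| 2 SD | 51.6% | 62% |
| 2.5 SD | 70.5% | 92% |
| 3 SD | 85.1% | 99% |

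If only one limit counts (2.5% on placebo, 16.9% after a 1 SD shift), the power is 2.8%.

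**Comparison of the numeric values.** ANCOVA on the screening value, by noncentral t with ncp = d / (√(1 − r²) × √(2/12)). Degrees of freedom are 48 − 5 = 43 using all four arms, or 24 − 3 = 21 using two. At d = 1 and r = 0.5, ncp = 1 / (0.866 × 0.408) = 2.83.

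| r | ncp at d = 1 | Power, 21 df | Power, 43 df |
|---|---|---|---|
| 0 | 2.45 | 64.7% | 66.8% |
| 0.3 | 2.57 | 68.8% | 70.9% |
| 0.5 | 2.83 | 76.9% | 79.0% |
| 0.6 | 3.06 | 83.1% | 84.9% |
| 0.7 | 3.43 | 90.5% | 91.8% |
| 0.8 | 4.08 | 97.3% | 97.9% |

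A simulation of the two-arm ANCOVA (20,000 trials per setting) gave slightly less: 75, 81, 89 and 97% for r = 0.5, 0.6, 0.7 and 0.8. Restricting screening values to the normal range hardly changed this (75, 82, 89 and 97%).

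**Precision.** With 43 df, the 95% half-width is 2.017 × √(1 − r²) × 0.408 SD. That is 0.82 SD at r = 0, 0.71 SD at r = 0.5 and 0.49 SD at r = 0.8.

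**The case against.** **This belongs to the analysis plan.** Section 11.1 defers detail to a statistical analysis plan that is not at hand, and it may add a model for the numeric values. That would be decisive if the protocol were silent. It is not: it fixes the form of the endpoint and states the test in several places.

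**A group shift would still be seen.** A reader might infer that a 1 SD shift would go unnoticed in the report. The documents do not support that. Section 11.1 plans means and standard deviations for continuous variables, and section 8.1.1.1 sends laboratory results that meet adverse-event criteria into adverse-event reporting. What stands is narrower: those summaries give no dose-minus-placebo difference, no interval and no use of the screening value.

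**The contrast depends on the shift chosen.** This is correct. At 1 SD about 83% of vaccinees remain within range, and whether such a shift matters is a clinical judgement. For shifts of 2.5 SD or more, Fisher's test is adequate. Section 11.3 does not size the trial for comparisons between arms.

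**If the results are not to be read as tests, power is the wrong measure.** This is partly right. Power shows how little information the planned comparison keeps; the practical gain is an estimate with an interval.

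**Vital signs.** A reader might extend the point to vital signs, through the general Fisher sentence. The documents do not support this. The endpoint lists contain no normal/abnormal vital-sign endpoint, the Synopsis says vital signs are summarised by group, and section 5.1.5.5 lists only oral temperature at the Day 21 and Day 42 visits.

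**Conclusion.** The point holds for haematology and biochemistry. The protocol states a valid but very insensitive comparison for data that support a better one. For an assumed 1 SD shift at 12 per arm, Fisher's test has about 2% power. A continuous comparison has about 65 to 71% with a screening correlation of 0 to 0.3, and 77 to 98% with 0.5 to 0.8. The conclusion does not hang on the correlation, since even at zero the difference is about thirtyfold (64.7 / 2.2 = 29).

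The figures are conditional on normality, a central-95% range, full follow-up and the size of the shift. The protocol gives no laboratory effect size, abnormal rate or correlation, so they illustrate the loss and are not properties of this trial. The trial can run as it stands, but the comparison should be improved before the data are analysed.

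**What to change.** Keep the normal/abnormal tables: they are needed to identify individual outliers. Add to section 11.1.2.2, for numeric haematology and biochemistry results, an ANCOVA of the Day 21 value and of the Day 42 value (log scale where skewed) on dose group, with the subject's screening value as covariate and all four arms in the model. Report each dose minus placebo with a 95% confidence interval. State that these are estimates and not significance findings.

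The cost is extra tables from data already collected. Section 7.1.1 lists about 28 analytes (13 haematology and 15 biochemistry, counting ALT and SGPT as one). Hence 28 × 2 visits × 3 doses = 168 intervals, of which about 168 × 0.05 = 8 would exclude zero by chance if the vaccine had no effect. The report should say so beside the tables. Section 11.1 already declines multiplicity control, so no other change is needed.

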8.1.1.2 Secondary Endpoints

Geometric mean titres: (GMTs) of hemagglutination inhibition (HAI) antibody will be evaluated on Day 0, Day 21, Day 42. Follow-up serology samples for GMTs will be taken at Day 228. GMTs will be analyzed as follows:

- Seroconversion factor or GMFR (Geometric Mean Fold Rise): is the geometric mean of the ratio of GMTs (Day 21/Day 0 and Day 42/Day 0).
- Seroconversion rate: the proportion of subjects in a given treatment group with either a ≥ 4-fold increase in reciprocal HAI titres between Day 0 and Days 21 and 42; or a rise of undetectable HAI titre (i.e. < 10) pre-vaccination, (Day 0) to an HAI titer of ≥40 at Day 21 and 42 post-vaccination.
- Seroprotection rate: the proportion of subjects in a given treatment group attaining a reciprocal HAI titer of ≥40 at 21 and 42 days post-vaccination (the percentage of vaccine recipients with a serum HAI titer of at least 1:40 following vaccination).

8.1.1.3 Exploratory Endpoints

The nature of the cell-based immune response will be assessed using two different methodologies:

- Flow cytometry will be used to assess the percentage and activation state of PBMC subsets following re-stimulation with vaccine antigen (and control antigen) in vitro (e.g. CD69 on lymphocytes, HLA class II on monocytes). Flow cytometry will also be used to assess intracellular cytokine production by antigen re-stimulated T cells (e.g. IFNγ production by CD8 cells).
- The profile of cytokines produced by PBMCs from subjects cultured in presence of vaccine antigen (vs. control antigen) will be assessed using multi-plex technology. The cytokines measured will include both Th1 type (IL-2, IL-15, IL-17, IFN-γ, and Th2 type (IL-4, IL-5, IL-6, IL-10, IL-13) as well as inflammatory/chemokine type (IL-1α, IL-1β, IL6, IL-8, TNF-α, RANTES). Antigen-specific lymphoproliferation will also be assessed using aliquots of these PBMC by either BrdU incorporation or CFSE.

8.1.2 Assessment Methods

These data are exploratory only and would not normally be included in any submission documentation. Straightforward statistical analysis (e.g: t-tests or ANOVA) will be used to compare the relative proportions of cells (e.g: CD4/CD8 rations) as well as the proportions of cells expressing particular activation markers or cytokines.

8.1.3 Handling of Missing Data and Outliers

8.2 Efficacy Endpoints and Assessment Methods

The EMEA (CHMP) has issued requirements (Note for Guidance on Harmonisation of Requirements for Influenza Vaccines), 12 March 1997 - CPMP/BWP/214/96, regarding the need to test annual modifications to influenza vaccine strains. The purpose is to verify the tolerance or incidence of adverse reactions and immunogenicity of the hemagglutinin of the vaccine strains, including the titer and frequency of anti-HA antibody responses.

In this clinical trial and in accordance with the most recent EMEA (CHMP) guideline entitled “*Guideline on Influenza Vaccines Prepared from viruses with the potential to cause a pandemic and intended for use outside of the core dossier context*,” February 2007 – EMEA/CHMP/VWP/263499/2006: “all three criteria (seroprotection rate, GMT increase and response rate) as defined below should be fulfilled.”

- Number of seroconversions or significant increase in anti-haemagglutinin antibody titer >40%;
- Mean geometric increase > 2.5;
- The proportion of subjects achieving an HAI titer of ≥40 should be 70%

9.0 SERIOUS ADVERSE EVENTS

9.1 Reporting of Serious Adverse Events

A Serious Adverse Event (SAE) (experience) or reaction is any untoward medical occurrence (whether considered to be related to study vaccines or not) that at any dose:

- Results in Death;
- Is life-threatening (at the time of the event);
- *NOTE: The term “life-threatening in the definition of “serious” refers to an event in which the patient was at risk of death at the time of the event; it does not refer to an event which hypothetically might have caused death if it were more severe.*
- Requires inpatient hospitalization (≥ 24 hours) or prolongation of existing hospitalization (elective hospitalizations/procedures for pre-existing conditions that have not worsened are excluded);
- Results in persistent or significant disability/incapacity; or
- Is a congenital abnormality/birth defect.

Medical and scientific judgment should be exercised in deciding whether expedited reporting is appropriate in other situations, such as important medical events that may not be immediately life-threatening or result in death or hospitalization but may jeopardize the patient or may require intervention to prevent one of the other outcomes listed in the definition above. These should be considered serious. Examples of such events are intensive treatment in an emergency room for allergic bronchospasm, blood dyscrasias or convulsions that do not result in hospitalization, or development of drug dependency or drug abuse.

In the event of a clinically important adverse event, a suitable sample will be collected for drug assay or for additional laboratory tests. The Investigator must ensure that the sample is properly labelled and stored. The Investigator and others responsible for care of the subjects should institute any supplementary investigations of significant adverse events based on the clinical judgment of the likely causative factor. This may include seeking a further opinion from a specialist in the field of the adverse event.

9.1.2 Expectedness of an Adverse Drug Reaction

An “unexpected” adverse reaction is one, the nature or severity of which, is not consistent with information in the relevant source document(s). Until source documents are amended, expedited reporting is required for additional occurrences of the reaction.

9.1.3 Initial SAE Reporting by the Investigator

Serious adverse events related to pre-treatment study procedures will be reported from the time the Informed Consent is signed. All post-vaccination SAEs will be reported from the time of receiving the study vaccine through the Final Safety Visit, Day 228. The study Investigator must report via telephone, all SAEs, whether related to the test article or not, to the Medical Monitor, within 24 hours (one business day) of the Investigator’s learning of the event. The Investigator must also complete, sign and date the SAE report form, and fax a copy to:

[name].,

[contact] [contact]

[contact]

A copy must also be faxed to:

Attn: [name], Project Leader

Medicago R&D Inc.

[name]

[name]

[contact]

[contact] [contact]

9. 1.4 Follow-up Reporting by the Investigator

Serious adverse events, regardless of causality, will be followed to resolution until the event returns to the baseline condition, the event stabilizes, or if ongoing at Day 42, the SAE will be followed until resolution and until 30 days following the final safety visit on Day 228. Where appropriate, documentation of any medical tests or examinations performed will be provided to document resolution of the event.

9.1.5 Reporting of SAEs Occurring after Subject Trial Termination

All SAEs will be followed until resolution or for a period of 30 days from the final study visit on Day 228.

9.1.6 Causal Relationship

The Investigator must make the determination of relationship to the test article for each adverse event. The Investigator should decide whether, in his/her medical judgement, there is a reasonable possibility that the event may have been caused by the investigational vaccine. If there is any valid reason, even if undetermined or untested, for suspecting a possible cause-and-effect relationship between the investigational vaccine and the occurrence of the adverse event, then the adverse event should be considered “definitely related,” “probably related” or “possibly related”. Otherwise, if no valid reason exists for suggesting a possible relationship, then the adverse event should be classified as “probably not related.” The following guidance may be helpful:

**Probably Not Related**: There is no medical evidence to suggest that the AE is related to the test article. The event can be readily explained by the subject’s underlying medical condition or concomitant therapy or lacks a plausible temporal relationship to the test article.

**Possibly Related**: A direct cause and effect relationship between the test article and the AE has not been demonstrated but there is a reasonable possibility that the event was caused by the test article.

**Probably Related**: There probably is a direct cause and effect relationship between the AE and the test article. A plausible biologic mechanism and temporal relationship exist and there is no, more likely explanation.

**Definitely Related**: There is a direct cause and effect relationship between the AE and the test article.

The medical assessment of intensity will be determined by using the following definitions:

**Mild:** The adverse event is easily tolerated and does not interfere with usual activity.

**Moderate:** The adverse event interferes with daily activity, but the subject is still able to function.

**Severe:** The adverse event is incapacitating and the subject is unable to work or complete usual activity.

The outcome may be classified as resolved, ongoing, resolved with sequelae, or death.

